### Participants

All participants will be evenly recruited from six hospitals in Beijing, China: Xiyuan Hospital of China Academy of Chinese Medical Sciences, Dongzhimen Hospital, Beijing Obstetrics and Gynecology Hospital, Beijing Hospital of Traditional Chinese Medicine, Beijing First Hospital of Integrated Chinese and Western Medicine and Beijing University of Chinese Medicine Third Affiliated Hospital.88 participants will be recruited from every hospital. In order to let more patients see our recruitment, we will publicize the official account and website of WeChat, and put up posters in each subcenter.

#### Inclusion criteria

Participants are women aged 21–40 years old who have been diagnosed with infertility and one of the following diseases: anovulatory abnormal uterine bleeding, polycystic ovarian syndrome, hyperprolactinemia, luteinized unruptured follicle syndrome, corpus luteum insufficiency and ovarian insufficiency; who have been diagnosed with the TCM syndrome of kidney deficiency pattern and blood stasis pattern; who have regular sexual intercourse during treatment; and who voluntarily sign the informed consent.

#### Exclusion criteria

The study excludes participants who have infertility due to congenital reproductive system physiological defects or malformations; hereditary factors; oviduct defects; immune factors; uterine fibroids; adenomyosis or endometriosis; spouses with reproductive defects; severe abnormalities of the cardiovascular system, liver function, kidney function or hemopoietic system; or allergies to experimental drugs.

#### Discontinuation criteria

Treatment will be discontinued when the PI deems the trial harmful for the participant.

The whole trial will be terminated if the clinical trial is canceled by authorities or serious adverse events happen during the trial.

### Withdrawal criteria

Participant have the right to withdraw from the study, as defined in the informed consent document, or to “drop out” if they do not explicitly withdraw from the study but are no longer undergoing training and testing. The reason for withdrawal should be understood as far as possible and recorded, for example, perceiving lack of efficacy; intolerance of certain adverse effects; inability to continue the clinical study; and lost to follow-up without explanation. Case record forms for withdrawn participant will be kept, and the results of the last trial will be considered final.

### Diagnostic criteria of related diseases

Infertility is the failure to establish a clinical pregnancy after 12 months of regular, unprotected sexual intercourse, either primary or secondary [15].

#### Abnormal uterine bleeding-ovulatory disorders (AUB-O)

Uterine bleeding has no cyclicity or regularity, and the bleeding amount cannot be estimated. Anemia or hemorrhagic shock will mark severe cases.Excludes bleeding caused by pregnancy or pregnancy-related factors, bleeding after menopause, bleeding from the genital tract except the uterus or from nongenital organs, iatrogenic bleeding, and bleeding caused by systemic disease.Basal body temperature (BBT) appears as a single phase.One or more sex hormone levels are beyond the normal range, including follicle-stimulation hormone (FSH), luteinizing hormone (LH), prolactin (PRL), estradiol (E_2_), progesterone (P), and testosterone (T).

AUB-O will be diagnosed if both (1) and (2) are met and at least one of (3) and (4) is met [16].

#### Polycystic ovarian syndrome (PCOS)

Oligomenorrhea or amenorrhea: oligomenorrhea means a menstrual period > 35 days or < 8 cycles in the past 2–3 years after menarche, and amenorrhea means a duration of the menstrual period > 90 days. BBT shows a single phase.Clinical and/or biochemical hyperandrogenism. The features of clinical hyperandrogenism include crinosity and acne, and biochemical hyperandrogenism is defined as total testosterone (T) > 2.6 nmol/L and free testosterone ≥ 6.0 pg/mL.Polycystic ovarian morphology: Transvaginal ultrasound shows the presence of ≥ 12 antral follicles with follicle diameters ≥ 9 mm and/or ovarian volumes > 10 mL.

PCOS can be diagnosed if at least 2 of the 3 conditions are met [17].

#### Hyperprolactinemia

A fasting blood sample must be obtained between 9 and 11 a.m. when the patient is awake and calm. If the serum prolactin level is equal to or greater than 3 times the upper normal limit, which is 90 ng/ml, the blood test can be done only once. If the serum prolactin level is between 30 and 90 ng/ml, a second blood test is necessary. When the second serum prolactin level is still between 30 and 90 ng/ml, hyperprolactinemia can be diagnosed.Clinical manifestation: oligomenorrhea, amenorrhea, galactorrhea, infertility, etc.

Hyperprolactinemia can be diagnosed if (1) is met [18].

#### Luteinized unruptured follicle syndrome (LUFS)

Regular menstruation with double-phased BBT.Daily transvaginal ultrasound shows one of the following:
Small follicle luteinization type: follicle volume does not change on the estimated ovulation day, with the intrafollicular spot fading away;Follicle-retention type: follicle volume remains at 25 mm in diameter on the estimated ovulation day, and the wall of the follicle cyst thickens gradually. Strong echogenic dots appear 2–4 days from the estimated ovulation day and then fade away gradually.Follicle continuous enlarging type: the diameter of the follicle is 31–50 mm on the estimated ovulation day, without free fluid in the Douglas pouch.Fasting blood sample for assaying sex hormones shows that serum progesterone at the mid-luteal phase reaches the postovulation range.Qualified BBT, ultrasound image, and blood test result continue for at least two menstrual periods.

LUFS can be diagnosed if both (2) and (4) are met and at least one of (1) and (3) is met [19].

#### Corpus luteum insufficiency

Clinical features: The menstrual period is less than 21 days, or the menstrual phase is longer than 7 days with vaginal spotting before menstruation. Patients may have a history of early spontaneous abortion.BBT shows that the duration of the luteal phase is less than 11 days, or the descent of BBT from the high-temperature phase is flat.Fasting blood samples for assaying sex hormones taken 5–9 days before menstruation show that the serum progesterone level is lower than the normal range.

Corpus luteum insufficiency can be diagnosed if (1) is met and at least one of (2) and (3) is met [20].

#### Premature ovarian insufficiency

Oligo-/amenorrhea for at least 4 months.FSH > 25 IU/I on two occasions > 4 weeks apart.

POI can be diagnosed if (1) and (2) are met [21].

### Blinding

A central randomization system and random envelopes will be used to allocate patients. We will use a two-grade, double-blind, double-dummy design, and the first-grade blinding will ensure that all experimental drugs and control drugs have the same external packing so that both primary investigators and participants will not know which one the participant takes until the unblinding stage. The second-grade blinding refers to the random number and blinding code.

### Randomization

Using the stratified block randomization method, a special researcher at the Institute of Basic Research in Clinical Medicine, China Academy of Chinese Medical Sciences (IBRCM, CACMS) is responsible for compiling the number sequence table in turn, generating random numbers through SAS 9.3statistical software, determining them in the form of documents after coding, and keeping them by special personnel after sealing. According to the grouping results obtained, the clinical investigator gives the corresponding drugs to the patient according to the subject sequence number and drug number.

### Allocation concealment

The blind codes will be sealed and kept secure at IBRCM. The first-grade unblinding will be done before data analysis, and the second-grade unblinding will be done after we calculate the statistical results.

### Interventions

Eligible patients will be randomly allocated into one of the two arms. Experimental group: Bushen Culuan Decoction, containing the ingredients of Ligustrum lucidum, dodder, Xianling spleen, Morinda officinalis, Eupatorium adenophorum, Salvia miltiorrhiza, Angelica sinensis, Ligusticum chuanxiong, red peony, raw dandelion (made by Beijing Tcmages Pharmaceutical Co, Beijing) with clomiphene citrate placebo tablets (made by the drug manufacturing department of Xiyuan Hospital). Both drugs will be started on day 5 after a spontaneous menstrual period or after vaginal withdrawal bleeding following progesterone (100 mg twice a day for 6 days, Zhejiang Xianju Pharmaceutical Co, Taizhou) if the participant does not have a regular menstrual period. Bushen Culuan Decoction will be taken at 13 g three times a day for 14 days, while clomiphene citrate placebo tablets will be taken at 50 mg once a day for 5 days. Each treatment cycle will contain 3 menstrual periods. If the participant regains regular ovulation at the end of the first, her treatment will end, and if not, she will start the second treatment cycle. All treatments will be terminated after 2 treatment cycles. If the participant is pregnant, all treatment will be stopped, and she will be moved into the follow-up stage.

Control group: clomiphene citrate tablets with Bushen Culuan Decoction placebo treatment (made by Beijing Tcmages Pharmaceutical Co, Beijing). Clomiphene citrate tablets (Fertilan®, Codal Synto Ltd. Cyprus) will be taken at 50 mg once a day for 5 days, while Bushen Culuan Decoction placebo will be taken at 13 g three times a day for 14 days. The starting time, termination time, and treatment cycle will be the same as those of the experimental group.

### Study-specific visits and procedures

The whole experiment for every participant will involve treatment with Bushen Culuan Decoction+ clomiphene citrate placebo or clomiphene citrate+ Bushen Culuan Decoction placebo for three menstrual periods or six menstrual periods (Fig. 1). Every participant will attend up to five visits, including the screening visit, baseline visit, treatment visit, end-of-treatment visit, and follow-up visit. The overview of the study visits is shown in Table 1. All concomitant medications and adverse events will be recorded at every visit.

**Table 1 Tab1:** Overview of study visits

Overview of study visits								
	Screening visit	Baseline visit	Treatment visit				End-of-treatment visit	Follow-up visit
			1st and 2nd menstrual period	3rd menstrual period	4th and 5th menstrual period	6th menstrual period		
Physical examination	√							
Basal body temperature		√	√	√	√	√	√	
Fasting blood sample for safety profile		√					√	
Urine routine test for safety profile		√					√	
ECG for safety profile		√					√	
Pregnancy test*		√	√	√	√	√	√	√
Fasting blood sample for sex hormone steroids		√		√		√	√	
Transvaginal ultrasound for ovulation monitoring		√	√	√	√	√	√	
Blood sample for AMH and INHB		√					√	
Transvaginal ultrasound		√					√	
Coagulation indicator		√					√	
Traditional Chinese Medicine symptom score**		√	√	√	√		√	
Pregnancy and neonatal record								
Query for adverse events and concomitant medications		√	√	√	√	√	√	

Physical examination: weight and height for BMI; acne and hair observation

Fasting blood samples for safety profile: RBC, Hb, WBC, PLT, ALT, AST, BIL, BUN, Cr

Urine routine test for safety profile: WBC-M, RBC-M, PRO

Pregnancy test: will be tested if the high-temperature phase of BBT continues for more than 14 days in a menstrual period, or the menstrual period is longer than 28 days

^*^Degree of importance

Fasting blood samples for sex hormones: FSH, LH, PRL, E_2_, P, T

Transvaginal ultrasound: uterine and bilateral ovarian volumes, endometrial thickness and type, ovarian volume, antral follicle count, and sizes of ovarian cysts or developing follicles. Peak-systolic flow velocity, PI and RI of uterus and ovaries

Coagulation indicator: PT, TT, APTT, FIB

Traditional Chinese Medicine symptom score is shown in Table 2

*RBC* red blood cells, *Hb* hemoglobin, *WBC* white blood cells, *PLT* platelets, *ALT* glutamic-pyruvic transaminase, *AST* glutamic-oxalacetic transaminase, *BIL* bilirubin, *BUN* blood urea nitrogen, *Cr* creatinine, *RBC-M* red blood cells (high-power field), *WBC-M* white blood cells (high-power field), *PRO* protein, *FSH* follicle-stimulating hormone, *LH* luteinizing hormone, *PRL* prolactin, *E*_*2*_ estradiol, *P* progesterone, *T* testosterone, *PT* prothrombin time, *TT* thrombin time, *APTT* activated partial thromboplastin time, *FIB* fibrinogen *PI* pulsatility index, *RI* resistant index, *AMH* anti-Mullerian hormone, *INHB* inhibin B

*degree of importance

### Obtain signed informed consent

Every patient who agrees to participate in the study must sign the informed consent form (ICF). First, the clinical investigator will explain every detail relevant to the study to the potential participant, including the whole procedure; what the participant will do before, during, and after the treatment; the benefits and risks she will face; how to deal with any possible adverse events; making sure the participant fully understands the study. Every participant will get one copy of the ICF after signing it, and then she can move into the screening stage.

### Screening visit

Every participant who is willing to join in the study will have a face-to-face consultation with one of the clinical investigators to verify that they meet the basic inclusion criteria, such as age, reproductive history, and sexual intercourse condition. Those who are eligible will be scheduled for a screening visit.

Every participant will get a basal body temperature (BBT) form once she has joined the study. The BBT will be monitored and recorded on the form by the participant herself every morning from the day after the screening visit, and the result will be recorded in the CRF at every visit from the baseline visit.

### General history

Birth date (yyyy/mm/dd), height (to the nearest 0.1 cm), weight (to the nearest 0.1 kg), whether the participant has a physical job, and whether she is a smoker will be recorded.

### Fertility history

We will record the participant’s information, including the duration of infertility with normal intercourse, the number of pregnancies, the number of spontaneous abortions, the number of artificial abortions, and embryo damage.

### Menstrual history

The age of menarche, the durations of the menstrual period and menstruation, and the date of last menstruation period (LMP) of the participant will be recorded. We will also obtain information about the relevant treatment, including the treatment duration and medication she used.

### Diagnosis of the 6 diseases

The participant must have a diagnosis of one of the 6 diseases based on the diagnostic criteria mentioned above.

### Exclusion of other infertility factors of the couple

Every participant will be confirmed to have no congenital reproductive system malformation, uterine fibroid, adenomyosis, or endometriosis. The tubal patency and the semen quality of her partner will be confirmed to be satisfactory to get pregnant. Both the woman and her partner must have normal results of routine chromosome screening.

### Baseline visit

Each participant who is eligible for the study as screened in the last step will be scheduled for a baseline visit. We will collect general vital signs, safety index, and effectiveness index before the treatment in this stage.

### General vital signs

The general vital signs collected will include body temperature, pulse, respiratory frequency, and blood pressure (systolic blood pressure/diastolic blood pressure).

### Safety index

Fasting blood samples will be collected for testing routine blood tests, including RBC, Hb, WBC, and PLT. Liver and renal function tests will include ALT, AST, BIL, BUN, and Cr. A urine sample will be collected for WBC-M, RBC-M, and PRO. An ECG will be taken for routine heart function.

### Effectiveness index

The effectiveness index is divided into 6 parts.
The date and duration of LMP and BBT analysis. BBT will be analyzed by the clinical investigator, and the result will be categorized as single-phase, double-phase, or atypical double-phase, along with the duration of the high-temperature phase.Sex hormone. Sex hormones, including FSH, LH, PRL, E2, P, and T, will be taken one or two times before the baseline visit and will be recorded at the baseline visit. The first blood sample collection will be in the follicular phase of the menstrual period, which is days 3–5 of the menstrual period. The second blood sample collection will be at the ovulatory phase, as confirmed by a positive ovulation test result. If the participant does not have a typical menstrual period or cannot identify the ovulatory phase, she will take the blood sample once and record the date of LMP.Serum INHB and AMH. These two indicators will not significantly change within a menstrual period, so we will take them at the same time as the first collection of sex hormones.Coagulation indicators. Blood samples will be collected at the same time as the first collection of sex hormones in order to measure coagulation indicators, including PT, TT, APTT, and FIB.Transvaginal ultrasound. The first transvaginal ultrasound will be done 3–5 days after the menstrual bleeding has ended. The information collected at this time will be uterine and bilateral ovarian volumes, the thickness and type of endometrium, bilateral ovarian antral follicle count, uterine and bilateral ovarian peak-systolic flow velocity, pulsatility index, and resistance index. On the 12th day of the menstrual period, the participant will start to monitor the ovulation every day, and the size of the dominant follicle will be recorded.Traditional Chinese medicine symptom score. The clinical investigator will show the participant the form and explain every detail to ensure that the participant fully understands it and let her choose every answer. The form is shown in Table 2.

**Table 2 Tab2:** Traditional Chinese Medicine symptom score

Kidney deficiency pattern	Traditional Chinese Medicine symptom score standard (point)			
	0	1	2	3
	Never happened	Mild symptom or happened occasionally	Medium symptoms or happened sometimes	Severe symptoms or happened frequently
Amenorrhea				
Delayed menstruation				
Scant menstruation				
Weakness in lower back, waist and knees				
Dizziness and tinnitus				
sexual apathy				
Fatigue				
Colorless transparent urination				
Frequent urination at night				
Blood stasis pattern	Traditional Chinese Medicine symptom score standard (point)			
	0	1	2	3
	Never happened	Mild symptom or happened occasionally	Medium symptoms or happened sometimes	Severe symptoms or happened frequently
Feeling obstruction with menstruation				
Profuse menstruation with dark color				
Clot in menstruation				
Stabbing pain in lower abdomen area, may aggravating with sexual intercourse				
Dysmenorrhea				

After all the above information is recorded, the participant will be given a package of medication. The methods of taking the medicines are shown on the pack and will be explained by the clinical investigator. The clinical investigator will also instruct the participant on how to have effective intercourse during the ovulatory phase and how to deal with any possible problems she may face, then make an appointment for the next visit.

### Treatment visit

After getting the medication package, every participant will start medical treatment on day 5 of the 1st menstrual period and visit the clinical investigator on day 25 of the 1st menstrual period or on day 1 of the 2nd menstrual period if the menstrual period duration is less than 25 days. In every treatment visit, relevant information about the participant will be recorded, and she will be given the medication package for the next menstrual treatment period.

In the 1st and 2nd menstrual periods, the participant will start to monitor ovulation every day from the 12th day of menstruation, and the size of the dominant follicle will be recorded. If there is ovulation, a urine pregnancy test will be performed to exclude pregnancy. If there is no pregnancy, the treatment will be continued in the next period. The detailed medication use status, the date and duration of the last menstruation period along with BBT, and ovulation monitoring results will be recorded, and the traditional Chinese medicine symptom score will be evaluated.

In the 3rd menstrual period, serum sex hormones at the ovulatory phase will be tested and recorded in addition to all information collected in the previous period. If there is no ovulation, the blood sample for sex hormone testing will be collected on the 15th day of the menstrual period.

After treatment for 3 periods, we will analyze the ovulation of every participant. The participant will be considered to have regained regular ovulation successfully if she had ovulation in all of the past 3 periods. The treatment of the participant will be terminated, and she will have an end-of-treatment visit and then move forward into the follow-up stage. If the participant ovulates fewer than 3 times, she will go into the second treatment cycle.

For every participant in the second treatment cycle, she will have a 4th, 5th, and 6th treatment visit. The procedures of the 4th and 5th treatment visits will be the same as those of the 1st and 2nd visits, and the 6th visit will be the same as that of the 3rd visit. After the 6th menstrual period treatment, all participants will stop treatment and move into the next stage regardless of whether they recover regular ovulation.

If the participant gets pregnant in the treatment process, she will stop the treatment immediately and move into the end-of-treatment visit and follow-up stage.

### End-of-treatment visit

The information to be collected and the procedure will be the same as in the baseline visit, including general vital signs, safety index, and effectiveness index. If the participant is pregnant, the transvaginal ultrasound will be skipped. The clinical investigator will inform every unpregnant participant that she will be contacted by phone every 3 months to have a follow-up visit until she is pregnant or until 12 months after the end of treatment. If the participant is pregnant in the treatment or follow-up stage, phone follow-up will be continued until there is a pregnancy outcome.

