#### Statistical analysis

An independent statistician will use SPSS 21.0 (SPSS, Chicago, Illinois, USA) to analyze the data.

The mean ± SD will be used to describe normally distributed data, while medians with IQRs will be used if the data are not normally distributed. The *χ*^2^ test will be used for evaluating differences between dichotomous variables, while one-way analysis of variance or Student’s *t* test will be used for evaluating continuous variables. The Mann-Whitney test will be used if the data are not normally distributed. A *p* value < 0.05 will be considered statistically significant.

If there are dropouts from the study, the last-observation-carried-forward principle will be used to compensate for the loss of data.

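### End-of-treatment hormone, AMH, inhibin B and coagulation results include blood drawn in pregnancy, so an arm difference is a total effect and cannot be read as a direct drug effect

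*Protocol article*

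**What the plan says.** All from the protocol article.

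- **Treatment visit.** A woman who becomes pregnant on treatment is directed as follows: "she will stop the treatment immediately and move into the end-of-treatment visit and follow-up stage".
- **End-of-treatment visit.** The rule for what is done here reads: "The information to be collected and the procedure will be the same as in the baseline visit". This covers the laboratory outcomes, since they belong to the effectiveness index. The one exception for pregnancy is: "If the participant is pregnant, the transvaginal ultrasound will be skipped".
- **Effectiveness index (baseline).** For sex hormones, "The first blood sample collection will be in the follicular phase of the menstrual period, which is days 3–5 of the menstrual period", and a second sample follows at the ovulatory phase. AMH, inhibin B and coagulation go with the first sample. A woman without a typical cycle or an identifiable ovulatory phase is handled differently: "she will take the blood sample once and record the date of LMP".
- **Treatment visit, periods 3 and 6.** Sex hormones are sampled at the ovulatory phase. "If there is no ovulation, the blood sample for sex hormone testing will be collected on the 15th day of the menstrual period".
- **Table 1 and Secondary outcomes.** Sex hormones, AMH with inhibin B, and coagulation are all marked at the end-of-treatment visit, and all are secondary outcomes.
- **Statistical analysis.** Continuous variables are tested by "one-way analysis of variance" or Student's t test, with Mann-Whitney for non-normal data. No covariate is named.

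**The concern.** Pregnancy is the primary outcome, and the Background section hypothesises that the decoction raises it by promoting follicle development and ovulation. If that is right, the experimental arm will have more women whose end-of-treatment blood is drawn in pregnancy. Any marker that pregnancy shifts will then differ between arms even if the drug has no other action on it.

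The Background also cites an exploratory study that reported lower prolactin and higher estradiol with the decoction. A reader will want to know whether this trial confirms that as a mechanism. The end-of-treatment comparison as described cannot separate such a mechanism from its possible consequence, pregnancy.

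Periods 3 and 6 raise a related issue for sex hormones only. When the sample is taken depends on whether the woman ovulated, which is itself a response to treatment. That comparison therefore carries the ovulation effect.

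**Working it through.** **1. Which blood is drawn when**

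| Outcome | Baseline | Periods 3 and 6 | End of treatment, not pregnant | End of treatment, pregnant |
|---|---|---|---|---|
| Sex hormones | Days 3–5 and ovulatory phase; one sample if the cycle is atypical | Ovulatory phase, or day 15 if no ovulation | As baseline | Drawn; no day 3–5 exists |
| AMH, inhibin B | With first hormone sample | Not taken | As baseline | Drawn |
| Coagulation | With first hormone sample | Not taken | As baseline | Drawn |
| Transvaginal ultrasound | Done | Ovulation monitoring | As baseline | Skipped |

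The article does address pregnancy at this visit and exempts only the ultrasound. That pregnant women's blood is drawn therefore follows from a stated rule. Whether their results share one test with the others is not stated.

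**2. Group size for the illustration**

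The plan's 219 per arm (90% against 80%, α 0.05, β 0.10) is reproduced with one-sided α: 2 × 0.85 × 0.15 × (1.645 + 1.282)² / 0.10² ≈ 218.4, rounded up to 219. The article does not state sidedness. The figure is used here only as n.

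**3. Size of the distortion if all end-of-treatment samples are compared**

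Assumptions, none of them in the article: pE and pC are the proportions pregnant when sampled, pregnancy shifts the marker by k non-pregnant SDs, and the drug has no direct effect on it.

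- Mean difference: d = (pE − pC) × k
- SE = √{[2 + (pE(1 − pE) + pC(1 − pC)) × k²] / 219}
- Rejection rate at two-sided 5%: 1 − Φ(1.96 − d/SE) + Φ(−1.96 − d/SE)

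Example, 30% against 20% with k = 2: d = 0.20; SE = √[(2 + 0.37 × 4)/219] = √(3.48/219) = 0.126; d/SE = 1.59; rejection rate 0.36.

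| Pregnant, E vs C | k = 0.5 | k = 1 | k = 2 | k = 5 |
|---|---|---|---|---|
| 30% vs 30% | 0.05 | 0.05 | 0.05 | 0.05 |
| 25% vs 20% | 0.06 | 0.08 | 0.13 | 0.21 |
| 30% vs 20% | 0.08 | 0.16 | 0.36 | 0.60 |
| 40% vs 20% | 0.18 | 0.48 | 0.88 | 0.99 |

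On a ratio scale, if the level in pregnancy is m times the non-pregnant level at 30% against 20%, the ratio of arm means is (0.7 + 0.3m)/(0.8 + 0.2m): 1.6/1.4 = 1.14 at m = 3, 2.2/1.8 = 1.22 at m = 5, and 3.7/2.8 = 1.32 at m = 10. Both calculations concern means and do not describe a Mann-Whitney test.

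**4. What baseline adjustment gains**

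With correlation r between baseline and outcome, ANCOVA multiplies the residual variance by 1 − r²: 0.75 at r = 0.5 (1/0.75 = 1.33, equivalent to a third more patients) and 0.51 at r = 0.7. The article gives no r. A baseline sample of uncertain phase would lower it. This is a gain in precision only and does not remove the pregnancy component.

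**The case against.** The strongest reply is that the randomized comparison is valid as it stands. A hormone difference that arises through ovulation or pregnancy is part of what the drug does, and the trial's own hypothesis runs through ovulation. This is correct. A reader might infer that these outcomes re-measure pregnancy and ovulation instead of drug effect, but the documents do not support that. The contrast estimates a total effect, and with equal pregnancy rates the rejection rate stays at 5%. What remains is a limit on interpretation.

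Second, pooling is inferred. The article never says which visit, which sample or which women enter each test, and an analysis plan that is not shown could separate them. This also stands. It leaves the collection rules untouched, and it does not change the fact that the only tests named are unadjusted.

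Third, a reader might extend the cycle-phase point to every laboratory outcome. The documents do not support this. Coagulation, AMH and inhibin B are tied to the first hormone sample, and the article says AMH and inhibin B do not change significantly within a cycle. The single baseline sample in atypical cycles precedes treatment, so it adds noise and no bias between arms. The phase point is confined to sex hormones in periods 3 and 6. Those samples are timed at ovulation, before any conception in that cycle, so pregnancy affects them less.

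Fourth, unadjusted two-sample tests are valid in a randomized trial. Agreed: ANCOVA is an improvement and does not correct an error.

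Last, leaving out pregnant women conditions on the primary outcome. That is a real cost, so such an analysis can only be supportive.

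**Conclusion.** The point holds in a limited form. Followed as written, the end-of-treatment visit yields hormone, AMH, inhibin B and coagulation values from pregnant women, and the article names only unadjusted tests. If pregnancy rates differ by arm, a difference in these markers includes pregnancy and should not be reported as a direct hormonal or coagulation effect. Sex hormones in periods 3 and 6 likewise carry the ovulation effect.

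The documents do not determine the size. Over the assumed grid with unequal pregnancy rates, the rejection rate runs from 6% to 99%. It is close to nominal for small shifts and small differences in pregnancy, and exactly nominal when pregnancy rates are equal. These figures also assume that all end-of-treatment samples enter one mean-based test with 219 women per arm.

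Only secondary outcomes are affected; the pregnancy comparison is not. The change is worth making because it is cheap and prevents a misreading.

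**What to change.** 1. For secondary continuous outcomes, replace the unadjusted tests with ANCOVA on the baseline value already collected, on a log or rank scale if skewed, with disease as a factor.
2. Name pregnancy as an intercurrent event for the laboratory outcomes. Keep the all-randomized end-of-treatment comparison, label it a total effect that includes pregnancy, and report the number pregnant at sampling by arm beside it.
3. Add a supportive analysis without post-conception samples. For sex hormones, AMH, inhibin B and coagulation, compare day 3–5 samples with day 3–5 samples where both exist. State that this conditions on a post-randomization outcome.
4. Report ovulatory-phase and day-15 sex hormone samples from periods 3 and 6 separately, with the number of women in each by arm.

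The cost is wording in the analysis plan, with no new samples. The supportive analysis will have fewer women, because those who conceived are left out and some with atypical cycles have no day 3–5 sample. No causal claim can rest on it.
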